### Sample size

The sample size was calculated considering α = 0.05 (5% chance of a type I error), 1-β = 0.95 (% of sample power) and data from a visual analog scale (VAS) reported in the study by Pereira *et al*. [21]. The minimum number for each group was determined to be 15 individuals, to which 20% was added to compensate for possible dropouts during the study (total: 18 individuals per group). This calculation was performed using the G*Power software program [22]. Seventy-two individuals will be allocated to different groups (18 individuals per group) through a randomization process involving opaque envelopes containing cards stipulating one of the three following groups: A (2.62 Joules), B (5.24 Joules), C (7.86 Joules) and D (0 Joules).

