### Data analysis

Pain will be the primary outcome and will be determined using a VAS and algometer. EMG will be the secondary outcome. The independent variables will be the different light sources used for phototherapy. The dependent variables will be derived from the pre-treatment and post-treatment evaluations. Intra-group comparisons will be performed using repeated-measures analysis of variance (ANOVA or Friedman’s test), followed by either the Student’s t-test or Wilcoxon’s test. Inter-group comparisons will be performed using either one-way ANOVA or the Kruskal-Wallis test. The choice of tests will be determined by the distribution (normal or non-normal) of the data. The level of significance will be set to 5% (*P* <0.05). All comparisons and statistical analyses will be performed using the SPSS program, version 13.0 (Chicago, IL, USA). Cohen’s d will be employed to determine the clinical effect size of the proposed therapies, with the interpretation of the coefficients based on the classification established by Cohen [23]: 0.2 = small effect; ≥0.5 = moderate effect; ≥0.8 = large effect.

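### The within-arm pain tests drop anyone who misses a visit and the between-arm tests ignore the other visits; one mixed model would use every observed VAS value

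*Protocol article*

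**What the plan says.** The Abstract of the protocol article sets four assessments: baseline, immediately after, 24 h after and 48 h after a single session. The Background gives two hypotheses: that the highest dose reduces pain more than the lower doses, and that the effects of one session persist to 24 and 48 h.

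The Data analysis section makes pain (VAS and algometer) the primary outcome and uses two separate sets of tests:

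- **Within each arm, over time:** "repeated-measures analysis of variance" or Friedman's test, followed by Student's t-test or Wilcoxon's test.
- **Between arms:** one-way ANOVA or Kruskal-Wallis. No covariate is named, and the article does not say outright that these tests are run visit by visit, though that is the natural reading.

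The Sample size section expects losses. It states that "The minimum number for each group was determined to be 15 individuals", and that "20% was added to compensate for possible dropouts during the study", giving 18 per arm and 72 in all.

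**The concern.** Classical repeated-measures ANOVA and Friedman's test both work on complete rows. A participant who attends baseline and the immediate assessment but misses 48 h contributes nothing to either, not even the values that were recorded. The plan expects such participants and names methods that discard them.

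The between-arm tests behave differently. They keep everyone who has the value being tested, but they make no use of that person's other visits or of the baseline VAS. If people in more pain are less likely to come back, those still present at 24 and 48 h are a selected group. An effective dose lowers pain, so this selection removes more people from placebo than from the active arms and shrinks the observed difference.

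The persistence hypothesis is most exposed. The selection is absent immediately after treatment and builds up over the later visits, so a constant true effect could look like a fading one.

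**Working it through.** **1. The plan's own figure.** 15 x 1.20 = 18 per arm, as stated. If exactly the added participants are lost, 3/18 = 16.7% are missing. A full 20% loss from 18 leaves 18 x 0.80 = 14.4.

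**2. Cost in power.** The article gives no effect size or SD, so the 15 cannot be re-derived. Solving backwards from 15 per arm, power 0.95 and two-sided alpha 0.05 (sidedness is an assumption) gives f = 0.554 for a four-group one-way ANOVA, or d = 1.364 for a two-group t-test. At those effects, power with 14 per arm is 93.3% (ANOVA) or 93.5% (t-test), against 95.0% with 15. Loss of power is therefore not the main issue.

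**3. Who enters each test if a participant misses only 48 h.**

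| Test | Uses this participant? |
|---|---|
| Within-arm repeated-measures ANOVA or Friedman, four visits | No, at any visit |
| Within-arm paired follow-up test, baseline vs immediate | It could, since it needs only two values |
| One-way ANOVA or Kruskal-Wallis, immediate | Yes |
| One-way ANOVA or Kruskal-Wallis, 24 h | Yes |
| One-way ANOVA or Kruskal-Wallis, 48 h | No |

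**4. Size of the selection effect.** None of these inputs is in the documents; all are assumptions: VAS SD 2 cm; within-person correlation 0.5 or 0.7; true top-dose minus placebo effect -1.5 cm at every post-treatment visit; about 17% dropout overall, occurring at 24 h and 48 h; log-odds of dropout 0.5 or 1.0 per cm of the last observed VAS; the same mechanism in every arm. Shortfall = (1.5 - |estimate|) / 1.5.

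| Between-arm comparison on observed data | Mean estimate (cm) | Shortfall |
|---|---|---|
| Immediate | -1.5, nobody lost | 0% |
| 24 h | -1.44 to -1.34 | 0.06/1.5 = 4% to 0.16/1.5 = 11% |
| 48 h | -1.40 to -1.24 | 0.10/1.5 = 7% to 0.26/1.5 = 17% |

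Dropout came out at 21-24% on placebo and 9-12% on active treatment, only because the treatment lowers pain.

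Within the placebo arm, restricting to completers moved the immediate change from a true -0.50 cm to between -0.56 and -0.66 cm. That overstates it by 0.06/0.50 = 12% to 0.16/0.50 = 32%.

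A likelihood-based model on all observed values gave -1.45 to -1.56 cm over 600 simulated trials per scenario. The simulation error is at least 2 x sqrt(2/18) / sqrt(600) = 0.027 cm, so that range is compatible with no bias.

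**5. When the bias vanishes or changes.** These runs assumed SD 2 cm, correlation 0.6, about 1/6 missing, and log-odds 0.25 to 1.0 per cm.

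- True difference 0, same mechanism in all arms: estimate about 0.
- True difference 2 cm, same mechanism: the 48 h completer estimate is 1.97 to 1.75 cm if missingness depends on earlier pain, and 1.95 to 1.58 cm if it depends on the unseen 48 h pain.
- True difference 0, but a mechanism that differs by arm (29% vs 17% missing): a spurious difference of about 0.12 to 0.20 cm.

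**The case against.** A reader might infer that, because repeated-measures ANOVA and Friedman's test need complete rows, the dose effect itself rests on completers only, and that immediate post-treatment data are lost from the comparison of doses. The article does not support that. It assigns those tests to comparisons within an arm and compares doses by one-way tests, which keep everyone observed at the visit analysed. Nothing is lost from the dose comparison immediately after treatment, so no gain in precision can be claimed there from recovering dropouts.

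Other points on the plan's side also carry weight:

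- **Low risk of loss.** Follow-up is 48 h after one session, participants and evaluators are blinded, and placebo participants are offered active treatment at the end. Actual dropout may be well below the allowance, and nothing in the article suggests a mechanism that differs by arm.
- **Direction.** With a common mechanism the between-arm bias is towards no difference, which is conservative for a claim of efficacy.
- **Assumed inputs.** The percentages come from a simulation whose conditions (normal data, dropout driven by observed pain) suit the mixed model.
- **Unseen documents.** Imputation before the ANOVA would avoid the complete-row problem. A rule for missing values may stand in the full protocol or analysis plan, and its absence from an article is no fault.

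The last point limits the criticism to the methods the article names, as they are classically run. It does not remove the point: the named tests fit poorly with a four-visit design that expects dropout, and a better method is available at little cost.

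**Conclusion.** The point holds in a limited form. The completers-only problem belongs to the within-arm tests, and these serve the persistence hypothesis. The between-arm comparison is sound immediately after treatment. At 24 h and 48 h it can be attenuated, by about 4-11% and 7-17% on the stated assumptions, if missed visits depend on earlier pain and a true effect exists. With no true effect and the same dropout mechanism in all arms there is no bias. The cost in power of the planned losses is small, about 95% to 93%.

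This is a worthwhile and cheap improvement, not an error that invalidates the trial. The size is uncertain because SD, effect, correlation and dropout mechanism are all assumed.

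**What to change.** For VAS, replace both the intra-group and the inter-group tests as the main analysis with one linear mixed model for repeated measures:

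- **Outcome:** the three post-treatment VAS values.
- **Terms:** arm, visit, arm-by-visit and baseline VAS.
- **Covariance:** unstructured within person.
- **Data:** every observed visit of every randomised participant, in the assigned arm.
- **Report:** each active-versus-placebo difference, and the differences between doses, at each post-treatment visit.

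This one model addresses both the dose comparison and its persistence to 24 and 48 h. Keep the non-parametric tests as a sensitivity analysis.

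The cost is a change of analysis wording and slightly more work for the statistician. No extra data are needed, because baseline VAS is already collected, and the Trial status section says the study is still recruiting. The model relies on data being missing at random given the observed values. It would not remove bias if missing a visit depends on the unseen pain at that visit.

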
The aim of the proposed study is to evaluate the effects of four different doses of phototherapy (0, 2.62, 5.24 and 7.86 Joules) on pain, activity of the masticatory muscles (massester and bilateral anterior temporal) and joint mobility in individuals with temporomandibular disorder (TMD). A further aim is to determine the cumulative effect 24 and 48 hours after a single session. The hypothesis is that individuals with TMD submitted to phototherapy with different light sources (LLLT and LED) contained in a single device with a dose of 7.86 will experience a greater reduction in pain and change in electromyographic activity of the masticatory muscles in comparison to individuals submitted to lower doses and the effects of a single session of phototherapy will be maintained for 24 and 48 hours.

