#### Initial evaluation

The individuals who meet the eligibility criteria will undergo an initial evaluation in the following sequence: VAS, algometry for pain and EMG analysis on the masseter and anterior temporal muscles.

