### Procedures

The proposed study will follow the recommendations of the Consolidated Standards of Reporting Trials (CONSORT) statement to ensure greater transparency and quality of the findings. The participants will receive information on the objectives and the eligibility criteria of the study, and will subsequently provide informed consent. For eligible participants, the evaluator will collect the baseline data prior to randomization. This evaluator will be blinded to the allocation of the patients to the different groups. The following assessment tools will be applied: 1) RDC/TMD questionnaire for the diagnosis and inclusion of the participants; 2) EMG; 3) VAS for pain; and 4) an algometer. Detailed descriptions of each of these tools are offered below.

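### The between-arm test carries no baseline covariate, although pain, pressure threshold and EMG are all measured before randomisation; ANCOVA would be more precise and would remove chance baseline imbalance

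*Protocol article*

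**What the plan says.** All places are in the protocol article.

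- **Data analysis, between arms:** "Inter-group comparisons will be performed using either one-way ANOVA or the Kruskal-Wallis test". No covariate, mixed model or group-by-time term is named.
- **Data analysis, within arms:** "Intra-group comparisons will be performed using repeated-measures analysis of variance (ANOVA or Friedman’s test", with paired follow-up tests. This is the only place where a stated test sets pre- and post-treatment values against each other.
- **Data analysis, analysed variable:** "The dependent variables will be derived from the pre-treatment and post-treatment evaluations". This does not settle whether the between-arm test uses post-treatment values or changes.
- **Data analysis, primary outcome:** "Pain will be the primary outcome and will be determined using a VAS and algometer". EMG is secondary.
- **Procedures and Initial evaluation:** "For eligible participants, the evaluator will collect the baseline data prior to randomization", and participants "will undergo an initial evaluation in the following sequence: VAS, algometry for pain and EMG analysis".
- **Background, hypothesis:** participants given 7.86 J "will experience a greater reduction in pain and change in electromyographic activity of the masticatory muscles in comparison to individuals submitted to lower doses".
- **Sample size:** alpha 0.05, power 0.95, at least 15 per group, raised to 18.

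**The concern.** The question is comparative and concerns reduction from a starting level. That level is measured before allocation for every outcome, yet the between-arm test has group as its only term. With 15 to 18 women per arm, mean baseline pain can differ noticeably by chance.

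A comparison of post-treatment values carries the fraction r of any baseline gap into the contrast, where r is the baseline to follow-up correlation. A comparison of changes subtracts the whole gap when only the fraction r should be removed, so it errs the other way by (1 − r). Both leave variance in the error term that the baseline value could explain.

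At stake are the power and precision of the dose comparisons, including those between active doses on which the hypothesis rests, and protection against an unlucky allocation. The choice of test is stated in the article itself, so it is not a detail left to an unseen analysis plan.

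**Working it through.** **Inputs.** From the article: four arms, 15 evaluable per arm (18 recruited), alpha 0.05, power 0.95. Assumed, because the article gives neither: r = 0.3, 0.5 or 0.7, and a smaller effect of f = 0.40 as an alternative to the planned one. Outcome variance is taken as equal at baseline and follow-up.

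**The article's own figure.** The 15 per arm cannot be reproduced, since no effect size or SD is printed. It can be inverted. If the calculation was a four-arm F test, 15 per arm with 95% power implies f = 0.554 (noncentral F, 3 and 56 df, noncentrality 60f²). The increase to 18 is 15 × 1.2.

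**Residual variance, in units of the post-value variance.**
- Post values: 1
- Changes: 2(1 − r)
- ANCOVA: 1 − r²
- ANCOVA relative to changes: (1 − r²) / [2(1 − r)] = (1 + r)/2

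| r | ANCOVA vs post values | ANCOVA vs changes |
|---|---|---|
| 0.3 | 0.91 | 0.65 |
| 0.5 | 0.75 | 0.75 |
| 0.7 | 0.51 | 0.85 |

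**Power with 15 per arm.** The effective f is f for post values, f/√[2(1 − r)] for changes, and f/√(1 − r²) with 55 error df for ANCOVA.

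| Effect | Post values | Changes, r = 0.3/0.5/0.7 | ANCOVA, r = 0.3/0.5/0.7 |
|---|---|---|---|
| f = 0.40 (assumed) | 71% | 55 / 71 / 92% | 75 / 84 / 95% |
| f = 0.554 (implied) | 95% | 85 / 95 / >99% | 97 / 99 / >99% |

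**Chance baseline gaps.** The standard error of a difference between two arm means is √(2/n) SD: 0.37 SD at n = 15 and 0.33 SD at n = 18.
- A given pair differs by more than 0.5 SD with probability 2[1 − Φ(0.5/√(2/n))] = 17% (n = 15) or 13% (n = 18).
- The 7.86 J arm differs by that much from at least one of the other three with probability 38% or 31%.

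**What a 0.5 SD gap does.** It shifts the contrast by 0.5r = 0.15, 0.25 or 0.35 SD for post values, and by −0.5(1 − r) = −0.35, −0.25 or −0.15 SD for changes. Given that gap, the rejection rate of a nominal 5% pairwise test (normal approximation) is:

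| n per arm | Post values, r = 0.3/0.5/0.7 | Changes, r = 0.3/0.5/0.7 |
|---|---|---|
| 15 | 5.9 / 7.2 / 8.0% | 7.7 / 7.2 / 6.4% |
| 18 | 6.2 / 8.2 / 10.1% | 9.2 / 8.2 / 7.0% |

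**Where ANCOVA does not help.** Simulating one contrast with 15 per arm, the ANCOVA interval was wider than the post-value ANOVA interval in about 19% of trials at r = 0.3 and about 69% at r = 0.1. Estimating the slope inflates the variance of a contrast by about 1 + 1/54 on average, so the expected gain over post values vanishes near r² = 1/55, that is r about 0.13. The ANCOVA power figures above leave out this 2%.

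**The case against.** - **The planned test is valid.** This stands. Randomisation keeps the unconditional type I error at 5%. A reader might infer that the planned comparison is biased, but the design does not support that: the distortion exists only conditionally, given an imbalance that happened to arise.
- **Baseline may be used after all.** This also stands. A reader might infer that baseline is ignored altogether. The sentence on dependent variables and the hypothesis of a greater reduction both leave room for change scores, which use baseline by subtraction. The defensible statement is that there is no baseline covariate in the between-arm test.
- **Power is already 95%.** True at f = 0.554 for post values, where ANCOVA adds only 2 to 5 points. That effect is very large, however. The gain matters if true differences, such as those between active doses, are smaller, or if changes are analysed and r is low.
- **r is unknown, and entry requires VAS above 3.** Restricting the baseline range may lower r. At r = 0.3 and f = 0.40 the gain over post values is only 4 points (71% to 75%), though 21 points over changes (55% to 75% before rounding: 54.7 to 75.3).
- **Large imbalance is not the expected result.** For one chosen pair, a gap above 0.5 SD has a 13 to 17% chance. The 31 to 38% figure covers three pairs.
- **Adjustment narrows every interval at no cost.** A reader might infer this, but it is false, as the simulation shows for low r.
- **Nothing else controls baseline pain.** The article describes opaque envelopes and mentions no stratification. As a condensed account it may omit it, so the point does not rest on its absence.

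**Conclusion.** The point holds as one of efficiency and of protection against chance imbalance, not of validity. The article names between-arm tests without a baseline covariate and leaves open whether post values or changes are compared. At each correlation examined from 0.3 to 0.7, ANCOVA has lower residual variance than both: by 9 to 49% against post values and by 15 to 35% against changes.

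The practical size depends on quantities the article does not give. It is small against post values at the implied planned effect. It is moderate to large at f = 0.40: 4 to 25 points of power over post values, and 4 to 21 over changes. The f = 0.554 figure itself assumes that the sample size came from a four-arm F test. The plan should be changed, but the trial is not invalid if it is left as it is.

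**What to change.** Replace the inter-group sentence in Data analysis with text to this effect:

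*At each post-treatment time, arms will be compared by analysis of covariance with arm as factor and the participant's own baseline value of the same variable as covariate, separately for VAS, pressure pain threshold and each EMG index. Adjusted mean differences with 95% confidence intervals will be reported.*

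An equally good alternative is one mixed model per outcome over the three post-treatment times, with arm, time, arm-by-time and the baseline value as terms. For non-normal outcomes, prespecify a rank-based ANCOVA in place of the unadjusted Kruskal-Wallis test. Either version also settles whether post values or changes are compared.

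Cost: one sentence, one degree of freedom, and possibly a slightly wider interval for an outcome whose baseline correlation is very low. No new data are needed, and visits and treatment are unaffected. The article reports the trial as still recruiting, so the change can be fixed before allocation is revealed to the statistician.

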### Ethics and data security

The proposed randomized, placebo-controlled, double-blind trial received approval from the Human Research Ethics Committee of the University Nove de Julho (Sao Paulo, Brazil) under process number 18032013.4.0000.5511 dated 6 June 2013. All individuals will be asked to provide written, informed consent prior to randomization, using standard forms. The trial is registered with the World Health Organization under Universal Trial in ClinicalTrials.gov under the number NCT02018770.

## Discussion

The findings are expected offer scientific evidence regarding the importance of an effective conservative treatment option for patients with TMD and assist physiotherapists in the clinical decision-making process when working with such patients. Although a number of studies in the literature have addressed different forms of treatment for TMD [24–27] including phototherapy [28, 29], gaps in knowledge remain in clinical practice regarding the use of different light sources (LLLT and LED), as well as the most effective, evidenced-based doses.

In a systematic review, Melis *et al*. [30] found considerable methodological differences among studies, especially with regard to the number of applications, duration and characteristics (wavelength and frequency) of LLLT, demonstrating the lack of standardized guidelines for effective treatment. Thus, there is a need for further in-depth investigations regarding the use of phototherapy for the treatment of myogenous TMD [24–27]. Pain is the main symptom of this condition and muscle and joint involvement are the most prevalent in the population [31], leading to limitations with regard to activities of daily living, such as eating, speaking, yawning and smiling, as well as a reduction in quality of life [32].

The study will contribute to the practice of evidence-based use of phototherapy in individuals with a myogenous TMD, and the effects of specific phototherapy parameters can help optimize treatment strategies for reducing and even eliminating the signs and symptoms of myogenous TMD. Data will be published after the study is completed.

## Trial status

The proposed study is currently in the recruitment phase, and individuals are being diagnosed with TMD using the RDC-TMD questionnaire.

## Abbreviations

EMG: electromyography
LED: light emitting diode
LLLT: low-level laser therapy
MHC: maximum habitual contraction
MVC: maximum voluntary contraction
OPC: overlap percentage coefficient
RDC/TMD: Research Diagnostic Criteria for Temporomandibular Disorders
RMS: root mean square
ROM: range of motion
TC: torque coefficient
TMD: temporomandibular disorder
VAS: visual analog scale.
